## 1. INTRODUCTION

### Background / State of Art

The management of endometriosis-associated infertility remains controversial (Vercellini *et al.*, 2014; Somigliana *et al.*, 2017; Hodgson *et al.*, 2020). Robust evidence has emerged only for superficial peritoneal endometriosis, a situation that cannot be identified without surgery. According to a recent Cochrane meta-analysis, odds ratio (OR) of viable intrauterine pregnancy in women undergoing laparoscopic treatment for superficial peritoneal endometriosis compared to diagnostic laparoscopy is 1.89 (95%CI: 1.25-2.86) (Bafort *et al.*, 2020). Despite this evidence, performing diagnostic laparoscopy in all women with unexplained infertility to identify and treat those with early stage endometriosis is questionable. The absolute increase in pregnancy is modest and, since endometriosis is present in only 30-50% of eligible women, at least half of the patients are uselessly exposed to the risks and costs of surgery. Overall, the value of care is low and diagnostic laparoscopy in women with unexplained infertility to identify and treat superficial peritoneal endometriosis is currently not recommended (ETIC, 2019).

Robust evidence for all the other forms of endometriosis is lacking. To date, there is no RCTs neither prospective comparative studies aimed at clarifying the potential benefits of surgery versus assisted reproductive techniques in women with more advanced endometriosis, in particular those carrying ovarian endometriomas or deep peritoneal lesions. Of interest here is that, in contrast to superficial peritoneal endometriosis, these forms of the disease can now be reliably diagnosed without the need of surgery. Transvaginal ultrasound in particular is easily available and considered highly accurate. According to a recent Cochrane meta-analysis, sensitivity and specificity of transvaginal ultrasound for the detection of ovarian endometriomas are 0.93 (95%CI: 0.87-0.99) and 0.96 (95%CI: 0.92-0.99), respectively (Nisenblat *et al.*, 2016).

For deep peritoneal endometriosis, they are 0.79 (95%CI: 0.69-0.89) and 0.94 (95%CI: 0.88- 1.00), respectively (Nisenblat *et al.*, 2016). In addition, the modalities for diagnosis are now standardized and shared in the scientific community (Guerriero *et al.*, 2016). In fact, surgery is no more considered essential for diagnosis. This recent recognition of the validity of the non-invasive diagnosis of advanced endometriosis represents an outstanding achievement and a cornerstone for a wiser management of the disease. Infertile women with endometriosis detected at ultrasound now face two therapeutic alternatives, surgery or *in vitro* fertilization (IVF). Surgery aims at increasing the chances of natural conception but the magnitude of this benefit remains controversial and women are exposed to the risks of the intervention, including the possibility of surgery-related

damage to the ovarian reserve (Somigliana *et al.*, 2015). IVF may be more effective, but costs are higher and unoperated women face some peculiar additional risks during the procedure and during the subsequent pregnancy.

Albeit extremely rare, severe pelvic infections can occur after oocytes retrieval in women with endometriomas and pregnant women with deep peritoneal lesions may face sudden and unpredictable severe spontaneous hemoperitoneum (Somigliana *et al.*, 2015). At present, the decision between surgery and IVF is shared and tailored to the patients taking into consideration pros and cons of both approaches and including in the discussion also the history of previous surgery, the presence of pain symptoms and effectiveness of medical treatment, women age, results of ovarian reserve testing and semen analysis. However, the unavailability of RCTs or at least robust prospective studies comparing the two strategies hamper the possibility to provide precise estimates and, not surprisingly, management drastically differ among centres.

## **2. OBJECTIVE/HYPOTHESIS**

In this study, we hypothesise that IVF could be more effective than surgery for the treatment of endometriosis-associated infertility in women with a sonographic diagnosis of the disease. The study is a non-blinded, randomized controlled trial. It is aimed at providing robust data to be used to take clinical decision as well as drawing national and international recommendations. We expect significant benefits for patients, physicians and the public health system.

### Specific Aim 1:

To evaluate the chance of a live birth within one year since the time of randomization between women allocated to surgery and those allocated to IVF.

### Specific Aim 2.1:

To compare the cost-effectiveness of the two approaches using the health care system perspective.

### Specific Aim 2.2:

To assess whether the systemic inflammatory milieu characteristic of endometriosis may have an impact on the IVF outcomes and on the quality of folliculogenesis and embryological development through the analysis of steroid hormones in follicular fluid and circulating extracellular vesicles (EV)-immune and miRNA signatures. This aim will be pursued through the characterization and analysis of circulating extracellular vesicles (EV) immunologic, proteomic and miRNA signatures and measurement of steroid hormones in follicular fluid.

### **3. EXPERIMENTAL DESIGN**

The study is a randomized controlled study comparing the chance of pregnancy between infertile women with sonographically identified endometriosis undergoing surgery and those treated with IVF.

The study is not blinded because it is not possible to carry out the treatments provided without the patient and the doctor becoming aware of it. The starting point will be the moment of randomization. Women who agree to participate in the study will be randomized to surgery followed by natural pregnancy research (arm 1) or to three complete cycles of IVF (i.e. three egg retrievals regardless of the number of embryo transfers) (arm 2). The patients, in both groups, will undergo the treatment in the shortest possible time, maximum 3 months. Only live births from pregnancies that began within 12 months of the start of randomization will be included in the primary results. The duration of 12 months was decided on the basis of data in the literature for which the majority of spontaneous pregnancies after surgery are expected within 9 to 12 months of surgery (Adamson and Pasta, 2010) and because the same period of time is necessary for carry out three complete cycles of IVF. Extending the period to two years would not provide any significant advantage for the recruited women, neither in the IVF arm nor in the surgery arm, as for both the chances of success are destined to progressively decrease.

As regards the secondary objectives, the economic analysis will be carried out using the data of the NHS applying the reimbursements of the Lombardy Region. The costs of hospital care (surgery, IVF procedures, treatment of any complications from surgery or IVF, obstetric care) will be calculated according to the regional reimbursements following the diagnosis groups. Drug costs will be included exclusively for drugs for which a reimbursement from the NHS is provided (mainly gonadotropins). Costs of infertility diagnosis will not be included as they are similar in the two arms. On the contrary, the additional costs necessary to cope with any complications from surgery or IVF and the costs necessary for the management of obstetric complications in the two arms (including neonatal care) will be included. In fact, differences in the course of pregnancies obtained by the patients placed in the two arms cannot be excluded. The main focus is on the cost of getting a live baby.

Finally, to achieve the secondary biological objectives, only women included in the IVF arm will be recruited for this part of the study. They will be matched, to a control group of women without

endometriosis, in a 1: 1 ratio based on ovarian reserve ( $\pm 0.2$  ng / ml in AMH), age ( $\pm 1$  year), starting dose of gonadotropins (same drug and identical dose) and study period. This part of the study will be carried out in two units (Coordinating Center and San Raffaele Hospital) with the aim of including the first 50 cases recruited and the related 50 controls. The women included will be subjected to:

- collection and isolation in peripheral blood of extracellular vesicles (IV) as the main mediators of the systemic inflammatory condition that can interfere with the results of IVF. These will be analyzed centrally at EPIGET Lab. EVs will be evaluated by: i) Nanoparticle Tracking analysis (NTA) to determine their total values and their distribution; ii) specific markers for the various lymphocyte populations by flow cytometry to evaluate the immunological origin; iii) miRNA profile and iv) proteomic analysis in a minor subset of samples (25 cases and 25 controls).

- collection of follicular fluids from egg retrieval and dosage of steroid hormones. Furthermore, the characteristics of the embryos will be related to the concentrations of steroid hormones in the follicular fluids. These will be analyzed centrally at UOS Environmental and Industrial Toxicology.

Inclusion criteria are as follows:

- Age < 40 years
- Pregnancy seeking for more than 12 months
- Regular menstrual cycle, i.e. mean cycle interval between 21 and 35 days
- Ultrasonographic diagnosis of ovarian endometriomas or deep peritoneal endometriosis.

Normal seminal analysis based on WHO criteria

- Absence of ureteral stenosis or intestinal subocclusive symptoms.

Even severe pain symptoms will not be exclusion criteria. Patients with pain symptoms destined for IVF will be treated for pain with hormone therapy (progestogen, estrogen-progestogen, or similar GnRH) until attempted. These therapies will be suspended only during the period necessary to carry out the IVF cycle. In case of non-resolution of painful symptoms, the patient will be referred for surgery but will be kept in the IVF arm ("intention to treat" analysis).

Inclusion criteria for biological analysis controls

Exclusion criteria are as follows:

- Previous surgery for endometriosis
- Previous IVF cycles
- Contraindication to pregnancy
- Hydrosalpinx
- Endometriomas with a mean diameter > 4 cm
- Submucosal fibroids or large intramural or subserosal fibroids ( $\geq$  5 cm).
- Doubtful sonographic findings that do not allow to reliably rule out malignancy.
- Obstacles to regular sexual intercourses (sexual disturbances or logistic problems)

#### Exclusion criteria for biological analysis controls

Egg retrieval for fertility preservation

Severe pain symptoms will not be an exclusion criterion. Women with these symptoms allocated to IVF will be firstly treated with proposed hormonal treatment (progestins, estroprogestins or GnRH analogues) to manage their pain prior to embark in IVF. These treatments will be transiently discontinued only during the IVF attempts. In case of pain-resistance to hormonal treatment, the woman will be scheduled to surgery but maintained in the IVF arm (intention to treat analysis).

The infertility work-up will include: semen analysis, serum assessment of AMH and a transvaginal assessment including also antral follicle count (AFC). The ultrasound assessment will be performed according to international recommendations (Guerriero *et al.*, 2016).

Women accepting to enter the study will be randomized to either surgery and then natural pregnancy seeking or a program of three complete IVF cycles (i.e. three oocytes retrievals regardless of the number of embryo transfers performed). The initial time point will be the time of randomization. Women of both study groups will initiate treatment (surgery or IVF) in a shortest delay, maximum 3 months. Only live birth pregnancies and initiating within a 12-months period starting from this time point will be included in the primary outcome. The duration of 12 months was decided because most natural pregnancies are expected to occur during the first 9-12 months after surgery (Adamson and Pasta, 2010) and this same duration of time is needed to perform three complete IVF cycles. Extending this duration longer (two years) would be useless for women scheduled to IVF and could be unfair for women allocated to surgery (the chances of success with IVF could be significantly reduced).

After surgery, patients will be informed about their chances of natural pregnancy using the Endometriosis Fertility Index (EFI) questionnaire (Adamson and Pasta, 2010). Women unsatisfied with the prospected prognosis will be allowed to access IVF earlier.

Since both approaches (IVF and surgery) are supported by the public health system, the study will not cover the financial resources required for treatments. Both approaches will be performed according to local standards.

Sample size calculation is based on the following assumptions: 1) expected success rate in the surgical group: 30%, 2) type I and II errors of 0.05 and 0.20, 3) difference in favour of IVF justifying the additional costs of the procedure of 20% (absolute rate of success of 50%). On these bases, the number of women to be randomized is 206 (103 per arm). Considering an expected rate of eligible women declining treatment of about 30%, the total number of women to be initially selected would be 300.

The economic analyses will be performed using the public health system perspective by applying the reimbursements used in Lombardy. Costs of hospital care (surgery, and IVF procedures, management of IVF or surgical complications, obstetrics care) will be obtained using local reimbursements of diagnosis related groups (DRG). Costs of drugs will exclusively include those that are reimbursed by the public health system (mainly gonadotropins). Costs of infertility assessments will not be included since considered similar in the two arms of the study. In contrast, we will include additional costs needed to handle complications of surgery or IVF in the two arms as well as those required for obstetrics management of complications (including neonatal assistance). Indeed, we cannot exclude differences in pregnancy course between the deviations (leaving natural pregnancy seeking after surgery earlier or deciding for surgery prior to complete the three IVF attempts or drop-out from IVF program without switching to surgery) will not justify exclusion. Somehow, even if less pure, evidence that will be obtained with our study will better stick to everyday clinical practice.

A main possible cause of reluctance to participate or deviation could be age and ovarian reserve testing. Indeed, there is an unproven tendency to over-estimate the detrimental effects of timing on the chances of IVF. Age and ovarian reserve are crucial for IVF success but the impact of a one-year delay is modest. For instance, in a recent theoretical model, we highlighted that even in women older than 35 years, a 6-months delay in the access to IVF is unremarkable (Somigliana *et al.*, 2020). Moreover, it is important to underline that the amount of ovarian reserve does not affect the chances of natural pregnancy (Somigliana *et al.*, 2015b) and one may speculate that surgery could be even wiser in women with reduced ovarian reserve. To note, a low ovarian reserve testing was shown to be poorly predictive of premature menopause (Depmann *et al.*, 2018). A specific seminar dedicated to the complex relation among age, ovarian reserve, natural pregnancy and IVF success

will be organized prior to initiate recruitment for all physicians who will be engaged in the study to prevent undue beliefs that could ultimately be deleterious for recruitment.

#### **4. PROCEDURES**

##### Interventions

Women accepting to enter the study will be randomized to either surgery and then natural pregnancy seeking or a program of three complete IVF cycles (i.e., three oocyte retrievals regardless of the subsequent number of embryo transfers that will be possible). Both approaches will be performed according to local standards. The initial time point will be the time of randomization. Eligible patients will undergo a first visit of screening. They will undergo a transvaginal ultrasound control, following international guidelines for the diagnosis of endometriosis (Guerriero et al, 2016). Women eligible for the study will be referred by care providers to a member of the research team who will describe the informed consent process. Details of the study will be explained to patients, including its main aims, procedures, temporal commitment, possible discomforts and risks, benefits. Recruitment will be on a voluntary basis with the right to withdraw from the study at any time; moreover, women will be informed that the decision to join the study protocol will not affect their possibility to shift to the other technique (surgery or IVF). Finally, informed consent will be illustrated and provided to the patients willing to participate. Operators will give patients the opportunity for questions and enough time to consider their participation. After two weeks, patients who will agree to enter the study will refer again to return the signed consent and to be randomized. During this visit, demographic and clinical characteristics as well as ultrasound findings will be recorded. Randomization will be organized centrally by Redcap (version for Fondazione IRCCS Ca Granda Ospedale Maggiore Policlinico, Milano : <https://redcap.policlinico.mi.it/>). The allocation sequence will be computer-generated. The allocation ratio will be 1:1. Randomization list will be stratified for the three participating centres. All patients, all caregivers and embryologists at the clinical departments will not be blinded to trial intervention allocation after inclusion. The progress of the study will be periodically monitored by an external monitor in order to verify the strictness of the data management.

Once randomized, both patients and physicians will not be blinded to the treatment arm. Women of both study groups will initiate treatment (surgery or IVF) in a shortest delay, maximum 3 months. After surgery, patients allocated in this arm, will be informed about their chances of natural

pregnancy using the Endometriosis Fertility Index (EFI) questionnaire (Adamson and Pasta, 2010). Patients allocated in IVF arm will undergo three complete IVF cycles (i.e. three oocyte retrievals regardless of the number of embryo transfers performed). Visits in both arms will be done every 3 months. Patients will be controlled about symptoms or new endometriotic lesions throughout ultrasound scans. Final visit will take place 12 months from randomization. If pregnant, women will be contacted even later to assess the evolution of pregnancy.

Even if patients will be informed and made aware about the importance of persisting in the allocated arm because inefficacy of treatment cannot be drawn prior to complete the whole course (surgery + 9-12 months of natural pregnancy seeking versus three completed IVF cycles), they will be allowed to switch to the alternative treatment at any time (pragmatic trial). However, for the analyses, they will remain in the originally allocated arm (intention to treat). A per protocol analysis will also be done, but this is not the primary intent. Reasons surrounding the decision to switch will be recorded. At the end of the study period (12 months), women failing to conceive will be counselled about the option to persist in the allocated arm versus performing the cross-over; i.e. women who will be allocated to surgery will be offered IVF and the other way around for those allocated to IVF.

Given the uncertainty regarding the willingness to participate to a RCT comparing two radically different approaches, we will propose to women refusing randomization to participate to a parallel study that will assess the same outcomes as those who will be randomized, even if the decision is taken by patients rather than being randomly sorted (*patient preference trial*).

For specific aim 3, only women scheduled for IVF will be included in this part of the study. Women included will be subjected to:

A. *collection and isolation of peripheral blood EVs* as mediators of systemic inflammatory conditions that may affect IVF outcomes. EVs will be evaluated for i) Nanoparticle tracking analysis (NTA) to determine total EV counts and size distributions; ii) Immunological origins targeting the immune system population markers by flow cytometry; iii) miRNA and iv) proteomic signatures.

B. *collection of the follicular fluid during oocyte retrievals* and assessment of the whole steroids cascade. Comparisons will be done between women with and without endometriosis. In addition, embryological variables will be recorded and correlated with steroid hormone concentrations.

Peripheral blood will be collected prior to initiate the IVF cycle and the plasma fraction will be used to purify EVs. Plasma will be centrifuged three times at 1000, 2000 and 3000 × g for 15 min at 4°C,

and the pellet will be discarded to clean the cell debris. The vesicles will be then concentrated by ultracentrifugation at  $110,000 \times g$  for 120 min at 4°C. In order to obtain intact EVs, samples cannot be frozen and specimens need to be processed within 3 days from blood drawing. This is the main reason for recruiting new subjects instead of starting from biobanked samples.

NTA will be used to determine total EV counts and size distributions. EVs will be characterized for immune signatures using the MACSQuant Analyzer flow cytometer (Miltenyi Biotec, USA). EV analysis by flow cytometry is quite challenging for the limited EV size. To evaluate EV integrity, sample aliquots will be stained with carboxyfluorescein diacetate N-succinimidyl ester (CFSE) at 37°C for 20 min in the dark. CFSE is a vital non-fluorescent molecule that can enter EVs, where intracellular esterases remove the acetate group and convert the molecule into the fluorescent ester form. Each aliquot of CFSE-stained sample will then be incubated with specific antibodies to investigate the possible cellular origin of EVs: Ab-CD14+ (monocytes/macrophages), Ab-CD127+/Ab-CD25+ (Tregs), Ab-CD4+/Ab-CXCR3+ (Th1 cells), Ab-CD4+/Ab-CCR4+ (Th2 cells). Quantitative multiparameter analysis of flow cytometry data will be performed using FlowJo software (Tree Star, Inc., Ashland, OR, USA). Following extraction of EV-miRNAs using the commercial miRNeasy Mini and RNeasy MiniElute kits (Qiagen, Frederick, MD, USA), miRNAome (754 miRNAs) will be analyzed by QuantStudio™ 12K Flex Real-Time PCR System (Thermo Fisher). miRNAs associated most closely with inflammation-related endometriosis will be further confirmed by real time PCR in the rest of the samples.

Regarding proteomic signature, EVs will be lysed, proteins will be quantified and digested. Samples will be injected in duplicate on an nLC-ESI-MSMS quadrupole Orbitrap QExactive-HF mass spectrometer (Thermo Fisher Scientific). Peptides will be separated on UHPLC Easy-nLC 1000 (Thermo Fisher Scientific) connected to a 25 cm fused-silica emitter of 75 µm inner diameter (New Objective, Inc.), packed in-house with ReproSil-Pur C18-AQ 1.9 µm beads. MS data will be acquired using a data-dependent top 15 method for HCD fragmentation. Survey full scan MS spectra (300–1650 Th) will be acquired in the Orbitrap with 60 000 resolution, AGC target 3e6, IT 20 ms. For HCD spectra, resolution will be set to 15 000 at m/z 200, AGC target 1e5, IT 80 ms; NCE 28% and isolation width 1.2 m/z. For quantitative proteomics, raw MS files will be processed with MaxQuant (version 1.5.2.8) using label-free quantification, searching against the database Uniprot\_cp\_human\_setting. The peptides and protein FDR will be set to 0.01; the minimal length required for a peptide will be six amino acids, and a minimum of two Label-free quantification (LFQ) intensity will be imported into Perseus (version 1.5.0.31) applying imputation and Z-score

transformation. Statistical analysis will be performed using t-test, Benjamini–Hochberg correction, FDR 0.05.

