### Study monitoring

In accordance with applicable regulations and good clinical practice (GCP), the monitor will periodically visit or contact the center. The duration, nature and frequency of these visits / contacts depend on the frequency of recruitment, the quality of the documents held by the center and their adherence to the protocol. They will be decided with the monitor.

Through these contacts, the monitor must:

- check and evaluate the progress of the study

- examine the data collected
- conduct the verification of the source document,
- identify each problem and related solutions.

The purposes of the monitoring activity are to verify that:

- the rights and welfare of the subject are respected
- the study data are accurate
- complete and verifiable from the original documents
- the study is conducted in accordance with the protocol and any approved amendments, GCP

and applicable regulations

The investigator must:

- give the monitor direct access to all relevant documentation
- devote some of his or her staff and time to the monitor to discuss the results of the monitoring

and any other possible aspects.

The monitor will contact the center prior to the start of the study to discuss the protocol and data collection procedures with the staff. In consideration of the length of the follow up (up to two years) and the recruitment period (12 months), no interim analyzes are foreseen (almost all the patients recruited will still be in progress at the time of the end of the recruitment).

Any decisions on the interruption or modification of the trial will be made in agreement between the PI and all the participants previously listed. In case of discrepancy we will proceed by vote, in case of a tie the PI's decision will prevail.

Since the study is funded by the Ministry of Health (Finalized research grant), no significant conflicts of interest are expected. However, the personnel involved in the study inevitably have personal conflicts of interest that will be collected and declared at the time of the drafting of the study.

The monitoring will be managed by an independent external monitor.

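### The last visit for all women falls on the day the primary-outcome window closes and later contact is written only for pregnant women, so conceptions in the final weeks may be missed.

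*Protocol*

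**What the plan says.** Section 3 (Experimental Design) defines the outcome by when the pregnancy starts: "Only live births from pregnancies that began within 12 months of the start of randomization will be included in the primary results". The same section repeats this after the eligibility criteria: "Only live birth pregnancies and initiating within a 12-months period starting from this time point will be included in the primary outcome". Neither statement says what event dates the start of a pregnancy.

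Section 4 (Interventions) sets the contacts. "Visits in both arms will be done every 3 months", and the stated content is that "Patients will be controlled about symptoms or new endometriotic lesions throughout ultrasound scans". No pregnancy test is mentioned for either arm. The schedule closes with: "Final visit will take place 12 months from randomization. If pregnant, women will be contacted even later to assess the evolution of pregnancy". Also at 12 months, "women failing to conceive will be counselled about the option to persist in the allocated arm versus performing the cross-over".

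Three other statements bear on the point:

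- Section 10 (Study monitoring) explains the absence of interim analyses by a follow-up of up to two years: "In consideration of the length of the follow up (up to two years) and the recruitment period (12 months".
- Section 6 (Study Duration) lists follow-up of cross-over patients up to study month 48.
- Specific Aim 1 words the outcome differently: "To evaluate the chance of a live birth within one year since the time of randomization".

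**The concern.** The window for a qualifying pregnancy and the schedule of universal contact end on the same day. A pregnancy that began shortly before may be invisible at that visit, and the only written trigger for further contact is being pregnant. A woman counted at month 12 as not having conceived, who goes on trying naturally, has no later contact assigned to her. If she had in fact just conceived and later delivers, her birth belongs in the primary outcome but may never be recorded.

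Loss that is equal across arms would mainly lower both rates. The worry is unequal loss. An IVF pregnancy follows a dated procedure at the treating clinic and a natural one does not. If that leads to better detection after IVF, the surgery arm loses more events and the comparison moves towards the trial's hypothesis that IVF is more effective. The undefined start of pregnancy adds to this: dating by last menstrual period or by embryo transfer can shift a pregnancy across the month-12 boundary by about two weeks.

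**Working it through.** **1. The plan's own figure.** Inputs from section 7: 30% versus 50%, type I error 0.05, power 80%. With pooled rate 0.40 and a two-sided test:

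n₀ = [1.960·√(2·0.40·0.60) + 0.842·√(0.30·0.70 + 0.50·0.50)]² / 0.20² = 93.0 per arm.

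With continuity correction: n = (n₀/4)·[1 + √(1 + 4/(n₀·0.20))]² = 102.8, so 103 per arm and 206 in total. The stated number reproduces exactly, but only with the correction (93 per arm without it).

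**2. How many surgery-arm conceptions fall in the last weeks.** From the Protocol: a 30% surgery rate and treatment starting within 3 months, so W = 9 to 12 months at risk. Assumed, because the Protocol gives no figure: the last 2 to 4 weeks go unrecognised (m = 0.46 to 0.92 months), all of these are lost in the surgery arm and none in the IVF arm. Three accrual curves:

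- Even: loss = 0.30·m/W. Smallest 0.30·0.46/12 = 1.15 points; largest 0.30·0.92/9 = 3.07 points.
- Constant hazard, h = −ln(0.70)/W: loss = 0.30 − [1 − exp(−h(W − m))]. This gives 0.96 points (W = 12, 2 weeks) to 2.60 points (W = 9, 4 weeks).
- Front-loaded with an assumed 4-month scale: loss = 0.30·{1 − [1 − exp(−(W − m)/4)]/[1 − exp(−W/4)]}. This gives 0.19 to 0.91 points.

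| Accrual | Loss, points | Women of 103 |
|---|---|---|
| Even | 1.2 to 3.1 | 1.2 to 3.2 |
| Constant hazard | 1.0 to 2.6 | 1.0 to 2.7 |
| Front-loaded | 0.2 to 0.9 | 0.2 to 0.9 |

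Over all three, the observed surgery rate would be 26.9% to 29.8% instead of 30%, and the planned 20-point difference would appear as 20.2 to 23.1 points. Section 3 says that chances of success decline progressively in both arms, which favours the lower part of the range.

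**3. Effect on the error rate.** Exact rejection probabilities at 103 per arm, nominal two-sided 5%, true rate 40% in both arms, loss in the surgery arm only:

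| Loss | Uncorrected test | Continuity-corrected test |
|---|---|---|
| None | 5.4% | 3.8% |
| 1.2 points | 5.7% | 4.1% |
| 3 points | 7.6% | 5.7% |

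The excess lies in one direction. For the uncorrected test at a 3-point loss, the chance of a false finding in favour of IVF rises from 2.7% to 6.8%.

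**4. Whether other text closes the gap.** The two-year figure in section 10 is a general length and assigns no contact to anyone. Section 6 covers women who cross over. Section 4 covers women who are pregnant. A woman who stays in her arm and is not known to be pregnant falls under none of them.

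**The case against.** A reader might infer that late conceptions are missed in the surgery arm, caught in the IVF arm, and that the design therefore favours IVF. The Protocol does not support that as a statement of fact:

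- One rule governs both arms, and no pregnancy test or transfer record is described for either. A transfer just before month 12 would be just as unconfirmed at the visit. Testing after transfer is plausible, but it is an inference.
- Arm is not route of conception. Women may switch at any time and are analysed as allocated, and those unsatisfied with their prognosis after surgery may enter IVF earlier. Some late surgery-arm pregnancies will come from IVF.
- Saying that follow-up ends is too strong. The condition of being pregnant is not limited to pregnancies recognised on the visit day, and a late conception could surface through counselling at month 12, cross-over follow-up or the collection of obstetric costs.
- The calculation assumes total loss in one arm and none in the other. If the start is dated by a positive test, much of the lag disappears, and operational dating may be fixed in an analysis plan that is not at hand.

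All of this stands against the claim of an established bias. It does not remove the gap: none of these routes guarantees that every woman's status at the end of the window is established. The timing of visits and contacts belongs in the Protocol.

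**Conclusion.** The point holds as a gap in ascertainment. As written, the contact schedule can misclassify women who conceive in the last weeks of the window, because the last universal visit coincides with the window's end and no later check is required. A bias towards IVF is possible, and is the likelier direction if detection differs by route of conception, but it is not established.

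The size is small beside the planned 20-point difference. The 0.2 to 3.1 point range is a worst case for 2 to 4 weeks of loss, resting on that assumed period, on loss confined to one arm, and on the accrual curve. It could matter for a borderline result and for the estimated magnitude of benefit, which the primary endpoint asks for.

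Specific Aim 1 is a separate inconsistency. If the birth itself had to occur within one year, conceptions late in the window would count in neither arm. That conflicts with section 3 and must be resolved for the follow-up rule to have a clear target.

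**What to change.** - **Section 4 (Interventions):** state that pregnancy status is confirmed in all randomised women, by the same method in both arms, through one telephone or record check some weeks after month 12 (for example about month 14). Every pregnancy that began by month 12 is then followed to delivery, however it was discovered.
- **Section 3:** define the start of pregnancy by one rule on a common scale, for example a conception date from early ultrasound or from gestational age at delivery, with transfer dates converted to that scale.
- **Specific Aim 1:** reconcile with section 3, so that only one definition of the primary outcome remains.

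The cost is one short extra contact for women not known to be pregnant at month 12. Later contact with pregnant women is already planned, and the sample size of 206 does not change.
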